**Physical activity breaks**
Two 3-minute PA breaks were added to mathematics and foreign language lessons. At the teachers’ request, prerecorded exercise videos were selected as the simplest format for implementing the PA breaks. Two different breaks were constructed from the Students on the Move program’s break exercise cards [58]. The breaks were planned to be versatile, including balance, locomotor skills, and strength exercises, and five cards per break were selected based on students’ preferences.The PA breaks were implemented in the classroom, with the first break taking place 25 minutes after the lesson began and the second break 50 minutes after the lesson began (Break 1: [59]; Break 2: [60]). The breaks were mainly performed individually with the whole class participating, while the final exercises of each break were completed in pairs. The PA breaks did not include mathematics or foreign language learning goals, and teachers designed the lesson content apart from the breaks.Before the measurements, teachers were instructed to rehearse the PA breaks with the students to familiarize both themselves and the students with the procedures.

Researchers held a 2-hour meeting to present the study, PAL method principles, and PA breaks to the teachers implementing the intervention. The PAL method (treatment 1) was similar for every group, but the lesson-specific content was designed by the teacher. This ensured that the lesson content was a part of the course learning objectives. Teachers had the opportunity to ask for assistance from research team members and were required to submit lesson plans. The PA breaks (treatment 2) were the same for every group, and teachers only needed to play them on the screen for the students. Because only some of the teachers and students were familiar with the different physically active classroom practices, the teachers were instructed to rehearse the PAL method and PA breaks with the students to familiarize themselves and the students with the methods before the measurements.

Given that the physically active lessons adhered to the national curriculum and consisted of tasks typical of students’ everyday lives, participation did not pose any risk beyond that of a regular school day. Despite the study’s hypotheses, PAL and PA breaks may cause negative effects, such as reduced situational engagement, alertness, or executive functions. These effects were measured and analyzed as part of the intervention outcomes, and subgroup analyses may reveal whether modifying factors are associated with perceived disadvantages.

The fidelity of the intervention was monitored by having each lesson observed by trained personnel, who recorded the course of the lesson and any deviations or unusual events. Apart from the addition of the second wave, no changes were made to the study protocol after trial registration, and no major deviations from the protocol occurred during the study.

#### Measurements

The majority of the measurements were performed as part of the lessons conducted by trained personnel. In the baseline measurement session, students’ executive functions (inhibition and working memory) and academic skills such as reading and math fluency and spatial visualization were measured. In addition, the devices (Axivity AX3 and Firstbeat Bodyguard 3 monitoring device) and instructions for measuring PA, sedentary time, stress, recovery, and sleep were distributed, and instructions for self-monitoring usual daily and hourly variations in alertness were given. Finally, personalized answer links to complete the background survey were sent to the students via email. Students completed the questionnaire in their free time.

Students wore the devices for two 4-to-5-day measurement periods (including the treatments). The first measurement period started straight after the baseline measurement session, or at the latest, in the morning 3 days before the first intervention lesson, and it ended in the morning after the first intervention lesson. The second measurement period started in the morning of the day before the second intervention lesson and ended in the morning after the last intervention lesson. Students also filled out an online alertness questionnaire 4 times per day (9 AM, 11 AM, 1 PM, and 3 PM) for 3 days. The timeline of the measurements is presented in Table 1.

**Table 1. T1:** Example of a timetable of the measurements^a^.

	Day 1	Day 2	Day 3	Day 4	Day 5
Week 1	Baseline measurements. The first measurement period starts (devices on)	Alertness self-monitored at 9 AM, 11 AM, 1 PM, and 3 PM (devices on)	Alertness self-monitored at 9 AM, 11 AM, 1 PM, and 3 PM (devices on)	Intervention lesson 1 (devices on)	Devices removed
Week 2	Second measurement period starts (devices on). Alertness self-monitored at 9 AM, 11 AM, 1 PM, and 3 PM	Intervention lesson 2 (devices on)	Devices on	Intervention lesson 3 (devices on)	Devices removed

a For one group, the measurements lasted two weeks. During the first week of the study, the devices (Firstbeat Life and Axivity) were distributed during baseline measurements and were put on the same or the following day. The devices were worn for 3‐4 days continuously and were removed the day after the first intervention lesson. During the second week of the study, the devices were put on the day before the second intervention lesson and removed the day after the third intervention lesson. The measurement period in the second week lasted 2‐4 days continuously, depending on the group’s schedule.

Measurements during the intervention lessons included a short initial survey, an executive function test, and an alertness questionnaire at the beginning of the lesson; 2 alertness questions during the lesson; and an alertness questionnaire, an executive function test, and a situational engagement questionnaire at the end of the lesson (Figure 3). The initial survey (2 minutes to complete), conducted on students' own computers through Visual Learning Environment (ViLLE), a widely used digital assessment and learning platform, included questions about the quality of the previous night's sleep, as well as the consumption of breakfast, lunch, caffeine, nicotine products, and PA before the treatment. Students also wore the Axivity AX3 and Firstbeat Bodyguard 3 monitors to assess PA, standing, sitting, stress, and recovery during the intervention lessons.

**Figure 3. F3:**
[figure not shown]
The structure of the intervention lessons. Measurements during the intervention lessons included a short initial survey, an executive function test, and an alertness questionnaire at the beginning of the lesson; two alertness questions during the lesson; and an alertness questionnaire, an executive function test, and a situational engagement questionnaire at the end of the lesson.

#### Main Outcomes

##### Alertness

Changes in alertness were assessed using the validated Karolinska Sleepiness Scale [61,62]. The Karolinska Sleepiness Scale is a single-item measure of subjective situational alertness on a 9-point scale (1=extremely alert, 9=extremely sleepy, fighting sleep). Students completed it on paper, and it took 0.5 minutes to complete.

##### Executive Function—Inhibition

Changes in executive function performance, particularly in inhibition, were measured during the treatments. Inhibition was assessed using a computerized, modified version of the Eriksen flanker task [63], in which participants completed up to 160 trials involving 5 horizontally aligned blue arrows presented in either congruous (the middle arrow facing the same direction as the flanking arrows) or incongruous (the middle arrow facing the opposite direction) conditions. Students were instructed to respond to the direction that the middle arrow was facing as quickly and accurately as possible. A fixed interstimulus interval of 1000 ms separated the trials. Accuracy (%) and reaction time for correct responses (ms) in congruent and incongruent trials were assessed. Students completed the flanker task on their own computers via the ViLLE platform, and it took 3 minutes. The task, although built on a different technology, mimics the NIH Toolbox version of the Flanker task, which has demonstrated developmental sensitivity and good test–retest reliability in both children and adults [64-66].

##### Situational Engagement

Situational engagement was assessed with the validated InSituations (InSitu) instrument [25]. The InSitu consists of 17 items rated on a 5-point scale (1=not at all; 5=very much) measuring (1) behavioral and cognitive engagement (7 items; eg, “How well did you concentrate during the lesson?”), (2) emotional engagement (3 items, eg, “How much did you like this lesson?”), (3) disaffection (3 items, eg, “How much did you do other things than the ongoing tasks and instruction?”), (4) competence experiences (2 items, eg, “How easy was the lesson for you?”), and (5) help seeking (2 items, eg, “How much did you ask for help from the teacher/another adult during the lesson?”). Students completed the InSitu on their own computers through the ViLLE platform, and it took 2 to 3 minutes to complete.

### Modifying Factors

#### Physical Load

To monitor physiological stress and recovery, students recorded a single-channel electrocardiogram to measure heart rate variability (HRV). HRV is measured as the time interval, in milliseconds, between two consecutive R-wave peaks (RR-Interval) in the electrocardiogram. The measurement was done using a Bodyguard 3 (Firstbeat Technologies Oy, Jyväskylä, Finland) and the Firstbeat Life app. The device was attached with self-adhesive single-use electrodes (Arbo H92SG). Participants wore the device around the clock, except for showering and water exercise. In the app, the students logged their activities in the supporting electronic diary.

Data were processed using Firstbeat research software. Firstbeat Life analysis is based on heart rate analysis software that identifies different physiological changes through HRV. Physiological recovery, stress, sleep, and PA were collected [67]. A score ranging from 0 to 100 was generated for each of the different physiological states for each day (morning to morning). A higher number represents a better score.

#### Mental Load

Mental load was assessed using questionnaires measuring study burnout and engagement as part of the background survey. The Student Burnout Inventory-9 [68] assesses study burnout through 9 items measuring exhaustion, cynicism, and inadequacy at school, rated on a 6-point scale (1=strongly disagree; 6=strongly agree). Meanwhile, Energy, Dedication, and Absorption-9 [69] assesses study engagement through 9 items, rated on a 7-point scale (0=not at all, 7=daily).

#### Physical Competence

Perceived physical competence was measured as part of the background survey using a questionnaire that included a modified Finnish version of the Perceived Physical Competence Scale for Children [70] and questions about the ability and desire to develop one’s own physical ability [71]. Altogether, they comprise 12 items rated on a 5-point scale.

#### Academic Competence

Perceived academic competence was assessed using a questionnaire including self-reported academic achievement score and self-perceptions (in math and foreign language) [72]. Perceived academic achievement score was assessed with a question “How would you rate your current academic performance in mathematics?*”* rated on a 4-point scale (1=excellent, 4=poor). Self-efficacy in math and foreign language was measured with 4 items (eg, “Mathematics/foreign language is an easy subject”) with a 5-point Likert scale (1=completely agree, 5=completely disagree).

### Other Study Variables

#### PA and Sedentary Time

To measure PA and sedentary time, students wore an accelerometer (AX3 [73]) on the anterior midline of either thigh. The accelerometer was attached to the skin using Opsite Flexifix transparent adhesive film (8 × 10 cm), with a piece of mesh between the monitor and skin to enhance breathability [74]. Envelopes including the monitor, detailed instructions including video link for how to attach the monitor, 5 pieces of adhesive film, and mesh swabs were delivered to participants face-to-face in a classroom. Data were collected with a 100 Hz sampling rate and a dynamic range of ±8 g.

Raw data were downloaded using OMGUI (version 1.0.0.45; Open Lab) [75]. ActiPASS (version 1.62) [76] was used to perform activity classification. Data were processed using the software’s default ProPASS settings, which have been validated to work well with children’s data as well as adults’ [77]. The start and end times, time at school, and intervention class times for each participant’s data were imported to ActiPASS using a diary file to inspect different time domains separately. The autocalibration function of the software was used. Activity was classified based on movement type: sleep, lie, sitting, standing, walking, running, stair-walking, cycling, but also based on the intensity of movement: sedentary, light, moderate, and vigorous PA.

#### Cognitive Functions and Academic Skills

To address baseline cognitive functions and academic skills, performance in the following tasks was evaluated through the ViLLE platform: the Choice Reaction Time task (as a warm-up task), the Sentence Reading Fluency task (assessing reading fluency), the Calculations task (assessing arithmetic fluency), the Digitized Corsi Blocks task (assessing working memory), the Spatial Relations subtask of the Woodcock-Johnson III Cognitive Assessment (assessing spatial visualization ability), and the Flanker task (assessing inhibition). Completing the tests took approximately 20 minutes. The tasks are described in more detail in Table S1 in Multimedia Appendix 1.

#### Background variables

The background survey was conducted electronically using Webropol software (Webropol Ltd, Helsinki, Finland), consisted of 55 questions and took a median time of 20 minutes to complete. The collected data included a comprehensive list of background variables: personal identifying information, age and sex, perceived health, height, weight, physical fitness, several questions on PA, sleep and wake-up times, nutrition, family form, parental socioeconomic questions, background academic performance in comprehensive school, and language syllabi in comprehensive school. Regarding the studies in upper secondary school, the questionnaire measured, for example, perceived performance and motivation in studies and diagnosed learning difficulties.

### Statistical Approaches

#### Analysis Plan

Generalized linear mixed-effects models will be applied to study the acute effects of the intervention on outcome measures. A cluster-randomized individual crossover design is assumed, that is, individuals serve as their own controls when the clusters (school classes) are crossed over the three intervention arms. This is the most efficient of cluster-randomized study designs [78]. The data will be analyzed according to intention-to-treat principles. Data lost due to participation withdrawals, student absences from measurement lessons, and missingness caused by other reasons will be multiply imputed in the analysis of primary outcome variables.

Within the analysis of main outcomes of classroom interventions (alertness, executive function, and situational engagement), the first analyses will quantify the main intervention effects on the outcomes. The main effects in generalized linear mixed-effects models will be adjusted for 3 levels of confounding factors. First, the factors that are consequences of the study design are taken into account (season, lesson time, subject, and group ID as a random intercept). Second, the student-level constant factors (sex, learning-related disabilities) will be included in the models. Finally, the third set of models will be additionally adjusted for individual lesson-specific factors (prelesson activities, baseline alertness, quality and duration of preceding sleep, preceding meals, smoking and caffeine intake, and menstruation status). The further manuscripts will study modifying factors for the intervention effects. The studied modifying factors are planned to include current physical and mental load, perceived physical competence, and perceived academic competence. The models will include corresponding or less extensive adjustments based on the observations of analysis of main intervention effects. Mplus and R statistical packages will be used.

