### Acute Effects of Physically Active Academic Lessons (Part 2)

#### Study Design and Participants

The effectiveness of physically active academic lessons among students was examined using a cluster randomized individual crossover trial conducted in two waves. In spring 2024, a total of 4 teachers of mathematics and foreign languages from 5 general upper secondary schools in Northern Ostrobothnia, who had participated in both the development project and the teacher interviews, were invited and agreed to implement the intervention. In autumn 2024, 2 schools from Central Finland were contacted, and a total of 5 teachers of mathematics and foreign languages from these schools expressed interest and agreed to implement the intervention. From a total of 17 eligible course groups of first- and second-year students, 168 students volunteered to participate in the study. These groups included 10 from schools in Northern Ostrobothnia (4 in mathematics and 6 in foreign languages), comprising 242 students, of whom 74 volunteered, and 7 from schools in Central Finland (4 in mathematics and 3 in foreign languages), comprising 200 students, of whom 94 volunteered. Students had the opportunity to withdraw from the study at any stage, and any data collected up to the point of withdrawal were retained as part of the research material. Eight students dropped out of the study.

Students in the same course group formed the clusters (mean cluster size 10, ranging from 1 to 18), which were randomized to undergo the 3 different treatments (lessons) in a different order. As there are 6 possible permutations of the 3 treatments, each cluster was allocated one of these sequences using a random number generator that sampled integers uniformly from 1 to 6. This procedure ensured randomized assignment of treatment order across the groups. After the trial, 30 voluntary students were invited to student interviews. This study followed the Consolidated Standards of Reporting Trials (CONSORT) statement (2025). The CONSORT flow diagram of the trial is presented in Figure 2.

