Assuming the variance structure as observed in the pilot study (Matikkavire), $\rho_{1}=0.31$ and $\rho_{2}=0.01,$ the design effect is $2\left(1-0.31-0.01\right)=1.36$ and the required sample is n=115 individuals to be crossed over the treatments. By assuming 33 students per class and a 70% student participation rate, we need to recruit five classes. To balance the design, we decided to recruit six classes such that two classes would have been randomized to each of the three intervention arms, where the order of treatments is rotated. As the number of volunteering participants per group remained lower than expected, more groups were invited, and eventually, the recruitment continued in a second wave in the autumn of 2024 to obtain the desired statistical power.

The forthcoming subgroup analyses (eg, sex-specific analyses) and moderation analyses (moderating factors will include physiological and psychological state, and physical and academic competence of the student) have less statistical power to detect medium interaction effects. Statistical power is approximated for subgroups by standard methods as discussed above, and for more complex moderation analyses by, eg, post data-collection Monte Carlo simulation. The post hoc power calculations are not used to determine sample size, but to support the confidence of the interpretation of the results of the moderation models.

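### Treatment order is drawn without balancing over lessons 1 to 3, and the stated list of design factors in the model omits lesson position

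*Protocol article*

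**What the plan says.** **Allocation.** Under Study Design and Participants (Part 2), "each cluster was allocated one of these sequences using a random number generator that sampled integers uniformly from 1 to 6". No blocking, stratification or balancing is described. The same section gives the size: "From a total of 17 eligible course groups of first- and second-year students, 168 students volunteered to participate in the study".

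**Model.** The Analysis Plan sets out three levels of adjustment. At the first, "the factors that are consequences of the study design are taken into account (season, lesson time, subject, and group ID as a random intercept". The second adds sex and learning-related disabilities. The third adds lesson-specific covariates such as baseline alertness, sleep, meals and caffeine. Position, period and sequence appear in none of them.

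**Earlier intention.** Sample Size Determination says "To balance the design, we decided to recruit six classes", with treatment order rotated across them. That schedule was overtaken when recruitment widened, and the article does not claim balance for the 17 groups.

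**Timing and measurement.** Under Measurements, "The second measurement period started in the morning of the day before the second intervention lesson", and the example timetable places lesson 1 in one week and lessons 2 and 3 in the next. Alertness and the flanker task are measured at the start and end of each lesson. The end-of-lesson set comprises an alertness questionnaire, "an executive function test, and a situational engagement questionnaire at the end of the lesson". Engagement has no start-of-lesson value. The flanker task is also part of the baseline battery.

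**The concern.** In a three-period crossover, period is the most direct consequence of the design, and it is missing from a list that is presented as covering such consequences. *Lesson time* most naturally means clock time: it stands beside season, the section on PA and Sedentary Time refers to "time at school, and intervention class times for each" participant in that sense, and alertness is self-monitored at fixed hours of the day. Season separates the two waves and not the lessons within a group.

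Position effects are plausible. Lesson 1 falls in a different week and device period from the other two. The flanker task is taken 1 + 3 × 2 = 7 times. Engagement has no prelesson value that could absorb a shift. For flanker and alertness, a prelesson value removes a constant shift between lessons, but not a within-lesson gain that shrinks with repetition. Baseline alertness is the only prelesson outcome value listed, and it enters only the third set of models.

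Randomisation makes the unadjusted contrast unbiased on average over possible draws. There is only one draw, however, and whole groups share an order, so student-level standard errors do not carry the uncertainty that the draw adds. A drift over lessons could move the estimate with no sign of it in the output.

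**Working it through.** **The plan's own figure.** n = 2(1.960 + 1.282)² / 0.50² = 84.06. The design effect is 2(1 − 0.31 − 0.01) = 1.36, and 84.06 × 1.36 = 114.3, which rounds up to 115 as stated. The present point does not change that figure.

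**Inputs from the article.** 17 groups (10 with 74 students, 7 with 94), group sizes 1 to 18, correlations 0.31 (student) and 0.01 (group), and an independent uniform draw of one of six sequences.

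**Assumptions.**
- Group sizes matching those totals: 1, 4, 5, 6, 7, 8, 9, 10, 11, 13 in wave 1 and 10, 11, 12, 14, 14, 15, 18 in wave 2.
- Variances 0.01 (group), 0.31 (student) and 0.68 (residual).
- Complete data and no true treatment effect.
- A linear trend of b SD per lesson, because the article gives none.

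**Imbalance.** For one group, the PAL-minus-control position difference is ±1 with probability 4/6 and ±2 with probability 2/6, so its variance is (4/6)(1) + (2/6)(4) = 2. The SD of the mean difference over 17 equal groups is √(2/17) = 0.343. Weighted by students, with Σn² = 1968, it is √(2 × 1968)/168 = 0.373. Simulating 400,000 draws gives SD 0.374, median absolute value 0.256 and 95th percentile 0.726. In a separate simulation counting groups equally, all three treatments had the same mean position in only about 1.6% of draws.

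**Shift in the unadjusted PAL-control contrast** (b × multiplier):

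| b | Median (× 0.256) | 95th percentile (× 0.726) | 95th percentile as share of 0.50 |
|---|---|---|---|
| 0.1 | 0.03 | 0.07 | 15% |
| 0.2 | 0.05 | 0.15 | 29% |
| 0.3 | 0.08 | 0.22 | 44% |

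**Type I error at nominal 5%** (20,000 simulated trials per scenario):

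| Scenario | Student intercept, no position | Group intercept only, no position | Student intercept, with position |
|---|---|---|---|
| No trend | 4.8% | 1.8% | 4.9% |
| 0.1 per lesson | 7.0% | 3.1% | 5.2% |
| 0.2 per lesson | 11.9% | 6.7% | 4.9% |
| 0.3 per lesson | 19.4% | 13.1% | 5.3% |
| Lesson 1 alone differs by 0.3 | 10.7% | 5.9% | 5.2% |

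**Hand check at b = 0.2, no position term.**
- True SD of the estimate: √(2 × 0.68/168 + (0.2 × 0.373)²) = √(0.00810 + 0.00558) = 0.117.
- Student intercept: the trend adds b² = 0.04 to the residual variance, so the model reports √(2 × 0.72/168) = 0.0926. The effective critical value is 1.96 × 0.0926/0.117 = 1.55, a two-sided error of 12.1%.
- Group intercept only: the residual variance is 0.31 + 0.68 + (2/3)(0.04) = 1.017, so the reported SE is 0.110. The critical value is 1.84, an error of 6.5%.

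Both agree with the simulation.

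**Cost of the term.** With no trend, adding position multiplies the variance of the contrast by 1.055 (median) or 1.086 (mean), and the SD goes from 0.089 to 0.093. With a trend of 0.2 per lesson, the adjusted estimate is the more precise one: SD 0.093 against 0.116.

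**The case against.** The strongest reply is that the omission turns on an undefined term. *Lesson time* could have been meant as order in the series, and a condensed article may leave the coding of period to an analysis plan. The ambiguity is real. But the article does not defer the matter: it spells out three covariate sets, down to caffeine and menstruation status. If position was meant, clock time is then unlisted. Either way the text needs correcting.

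Second, the larger error rates assume a student intercept, which the list does not name either. With the group intercept alone the test is conservative at 0.1 SD per lesson, a little above nominal at 0.2 and clearly inflated only at 0.3. This stands, and both versions are shown. The low rates arise because that model overstates the within-student error. This offsets the inflation by accident and does nothing about the shift in the estimate.

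Third, alertness and inhibition are described as changes within a lesson, so a constant shift between lessons cancels. This also stands. The simulated figures apply most directly to engagement, and no pre-post scenario with a diminishing practice gain was simulated.

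Fourth, no trend has been shown, rehearsal of the methods and a baseline flanker session may reduce one, and the realised sequence counts are not in the text (the flow diagram is not visible). These points limit how much harm can be asserted. They do not explain why period should be left out.

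**Conclusion.** The concern holds. The draw does not balance treatments over lesson position, and the stated adjustment sets do not include it. What can be said is that balance is not assured and the model as listed would not correct a lack of it; actual imbalance cannot be shown.

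The size depends on the assumed trend. At 0.1 SD per lesson the effect is small. At 0.2 to 0.3 SD, type I error is 11.9% to 19.4% with a student intercept, or 6.7% to 13.1% with the group intercept alone, and an unfavourable draw can shift the contrast by 29% to 44% of the planned effect. The figures rest on the assumed group sizes, complete data and a common linear trend, and bear most directly on engagement. This is a change that should be made, with medium confidence in the extent of the harm.

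**What to change.** - Add lesson position (1, 2, 3) as a categorical fixed effect to the first adjustment set, so that it enters every main-effect model for alertness, inhibition and engagement. Include it in the imputation model too.
- Define *lesson time* as clock time. If it was meant as position, say so and list clock time separately.
- Show results without the position term as a sensitivity analysis.
- Report the number of groups and students per realised sequence, by wave.
- Add a clause to Sample Size Determination saying that the six-class rotation was replaced by the independent draw.
- Date the change relative to the start of outcome analysis, and label it as made after data collection.

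The cost is two parameters per model and no new data. If there is no position effect, the contrast loses about 5% to 9% in variance. On the plan's own figure, 115 × 1.086 ≈ 125 students would then be needed, against 168 recruited and 160 after the eight dropouts.
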